## VIII. Serious adverse events

### 1. Definition:

The mechanisms for reporting and notifying SAE are based on the guidelines adopted by the ICH-GCP. As defined by the WHO International Drug Monitoring Centre (1994), an SAE is any untoward medical occurrence that:

- 1) Causes death;
- 2) Is life-threatening (i.e. the patient was at risk of death at the time of the event; it does not refer to an event that might hypothetically have caused death had it been more severe).
- 3) Needs hospitalization or extension of hospitalization.
- 4) Causes persistent or significant disability or incapacity.
- 5) Results in congenital anomaly or birth defect (NB, females in the study population are likely to be post-menopausal).
- 6) Is a major medical event judged by the PI that is not immediately life-threatening and does not result in death or hospitalization but may jeopardize the patient or may require intervention to prevent one of the other outcomes listed above.

Note: the following situations are not reported as SAEs:

- 1) Scheduled elective surgery before signing the informed consent for this study;
- 2) Hospitalization required by routine health examination (such as routine gastrointestinal endoscopy);
- 3) Hospitalized for neurological rehabilitation only.

Unexpected adverse reactions (UARS) are adverse reactions that do not conform to the drug instructions. Suspected unexpected serious adverse reaction (SUSAR) is an unexpected adverse reaction at any dose, which:

- 1) Causes death
- 2) Is life-threatening (i.e. the patient was at risk of death at the time of the event; it does not refer to an event that might hypothetically have caused death had it been more severe)
- 3) Needs hospitalization or extension of hospitalization
- 4) Cause persistent or significant disability or incapacity
- 5) Results in congenital anomaly or birth defect.

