## **2. Record and report on SAEs**

An SAE form must be used to record the details of the event, and this will include a full description of the event, classification of the event using the above definitions, the PI's opinion on the causal relationship to the randomized management group, and the timing of the event. All SAEs should be reported to the leading site within 24 hours after the event is recognized. To obtain further information, the principal investigator may need to submit a tracking report to record the results of SAEs. The principal investigator is responsible for reporting SAEs to the institutional ethics committee according to local regulations.

A SUSAR form must be used to record the details of the event, including the full description of the event, the classification of the event according to the above definitions, the judgment of the PI on the causal relationship between the SUSAR and the suspected drug, and the details of the suspected drug. All SUSAR should be reported to the leading site within 24 hours as soon as the event is recognized. The principal investigator may need to provide more details to supplement the initially reported serious adverse events, and the results of SUSAR must also be recorded. The principal investigator is responsible for reporting SUSAR to the IRB or management department according to local regulations or management requirements.

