## **3. Monitoring of SAEs**

The leading center will closely monitor all SAEs to understand the relationship between

SAEs and study procedures and protocols, or the clustering of similar events in a specific location. If there are too many special SAEs related to the protocol, the study protocol needs to be revised or the trial needs to be terminated early. In addition, beyond the planned interim analysis meeting, the leading center will submit all SUSAR information to the data safety monitoring board for review.

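### The SUSAR definition in VIII.1 repeats five of the protocol's six seriousness criteria and omits the sixth, so a suspected unexpected reaction serious only under that criterion is handled as an SAE but not as a SUSAR

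*Protocol*

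**What the plan says.** Protocol section VIII.1 states that "an SAE is any untoward medical occurrence that" meets one of six numbered criteria. The sixth reads in part "Is a major medical event judged by the PI that is not immediately life-threatening and does not result in death or hospitalization", and covers such an event if it may put the patient at risk or "may require intervention to prevent one of the other outcomes listed above".

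The same section then calls an adverse reaction unexpected if it does not conform to the drug instructions, and opens the SUSAR list with "Suspected unexpected serious adverse reaction (SUSAR) is an unexpected adverse reaction at any dose, which". Five numbered criteria follow. The last is "Results in congenital anomaly or birth defect". There is no sixth item and no pointer back to the SAE criteria.

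Section VIII.2 makes these definitions operative: the SUSAR form must record "the classification of the event according to the above definitions". Section VIII.3 adds that, outside the planned interim analysis meeting, "the leading center will submit all SUSAR information to the data safety monitoring board for review". For SAEs in general, VIII.2 says "All SAEs should be reported to the leading site within 24 hours after the event is recognized".

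**The concern.** The word serious has two meanings within one section. An event can be serious enough to be an SAE, be suspected to come from the drug, be unexpected against the drug instructions, and still not be a suspected unexpected serious adverse reaction. Nothing in the text suggests that this is intended, and the five shared items correspond one to one.

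At stake is how a particular kind of drug reaction is routed: one that is caught and treated before it produces any of the other listed outcomes. Section IV.3 describes the existing evidence on tirofiban in acute stroke as conflicting. Prompt drug-specific reporting of unexpected reactions is therefore a safeguard that the protocol evidently means to have. No sample size, power or error rate depends on this point.

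**Working it through.** No arithmetic beyond counting applies. The check compares the two lists in VIII.1 and then traces one event through the reporting rules.

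**Step 1. The two lists**

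| Criterion | SAE list | SUSAR list |
|---|---|---|
| 1. Death | yes | yes |
| 2. Threat to life | yes | yes |
| 3. Hospital admission or longer stay | yes | yes |
| 4. Lasting or significant disability | yes | yes |
| 5. Congenital anomaly | yes | yes |
| 6. Major medical event putting the patient at risk or needing intervention | yes | **no** |

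SAE criteria: 6. SUSAR criteria: 5. Shared: 5. In the SAE list only: 6 − 5 = 1.

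**Step 2. The event affected.** Take a reaction suspected to be due to tirofiban and not described in the drug instructions. It is treated on the ward, was never life-threatening, did not lengthen the stay and left no lasting disability. It meets criterion 6, so it is an SAE. It meets 0 of the 5 SUSAR criteria, so under VIII.1 it is not a SUSAR.

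**Step 3. What happens to it under each rule**

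| Rule | Applies to this event? |
|---|---|
| SAE form with full description and causality opinion (VIII.2) | yes |
| Report to the leading site within 24 hours (VIII.2) | yes, as an SAE; SUSARs have the same time limit |
| Report to the ethics committee under local regulations (VIII.2) | yes, as an SAE |
| Leading-center monitoring for clustering (VIII.3) | yes |
| Regular review of unblinded data by the safety board (XIII) | possibly; content and interval are not stated |
| SUSAR form: details of the suspected drug and causality to that drug (VIII.2) | **no** |
| SUSAR report to the IRB or management department (VIII.2) | **no** |
| Submission to the safety board beyond the planned interim meeting (VIII.3) | **no** |

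The loss is confined to the last three rows. On the first of these the two forms do differ: the SAE form asks for causality to the randomized management group, whereas the SUSAR form asks for causality to the suspected drug and for details of that drug.

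**The case against.** The strongest reply is that little is lost. The event is still reported to the leading site on the same 24-hour clock, still goes to the ethics committee, and is still watched by the leading center. VIII.3 ties protocol revision or early termination to SAEs related to the protocol, a category to which this event belongs. The safety issues that the protocol names are also captured elsewhere. Symptomatic intracranial hemorrhage and 90-day death are outcomes (VI.9), and gastrointestinal and urinary bleeding, thrombocytopenia and coagulation dysfunction are recorded for everyone at 24-72 hours (VI.10.5.1). All of this stands, and it limits the point to the three SUSAR-specific steps.

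A second reply is that many reactions needing intervention would lengthen the stay and so qualify under SUSAR item 3. That may be so. The documents do not say how often, and it does not help an event that leaves the stay unchanged.

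A third reply concerns timing. Version 3.1 is dated September 5, 2023, and XV ends follow-up in December 2023. With 90 days of follow-up, a last visit on December 31 implies randomization by about October 2. On that timetable a corrected definition would govern few new infusions, so most of the practical value lies in checking SAE forms already on file. This stands too.

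Three stronger readings are tempting, and the documents support none of them:

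- A reader might infer that such events go unreported or can never be seen by the board. The SAE rules in VIII.2 and VIII.3 and the board's regular review in XIII rule that out.
- A reader might put a figure on the missed SUSARs, or treat one criterion in six as a share of events. It is a count of list entries, and the protocol gives no reaction rates.
- A reader might hold that, because participants are already inpatients, the sixth criterion is the main way in which a reaction becomes serious in this trial. Item 3 also covers a longer stay, and nothing in the protocol shows how events would divide between the criteria.

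**Conclusion.** The inconsistency is certain and stands in the current text: six criteria for an SAE, five for a SUSAR, no cross-reference, and a SUSAR form that classifies events by those definitions. Its consequence is narrow. A suspected, unexpected reaction serious only under criterion 6 keeps all SAE reporting but loses the SUSAR form, the SUSAR report to the IRB or management department, and the submission to the board beyond the planned interim meeting.

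The size cannot be derived from the documents. Among the 100 patients planned for tirofiban (XI.4), the number of affected events may be zero to a few. This is an assumption, not an estimate. The conclusion rests on sites applying VIII.1 as written; a site that classified by the usual sense of serious would not produce the gap. The correction is worth making because it concerns a safety definition and costs almost nothing, not because a large number of events is known to be at risk.

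**What to change.** Reconcile the two lists in VIII.1. The simplest way is to define a SUSAR as a suspected, unexpected adverse reaction that meets any of the six SAE criteria. Adding criterion 6 to the SUSAR list has the same effect. Align the seriousness field on the SUSAR form. Then check the SAE forms already on file against the corrected definition and forward any that now qualify.

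The cost is one line in the protocol, one on the form, and a desk check of existing SAE forms. The downside is possibly a few more SUSAR reports. No treatment rule, outcome or analysis changes.

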## **2. Record and report on SAEs**

An SAE form must be used to record the details of the event, and this will include a full description of the event, classification of the event using the above definitions, the PI's opinion on the causal relationship to the randomized management group, and the timing of the event. All SAEs should be reported to the leading site within 24 hours after the event is recognized. To obtain further information, the principal investigator may need to submit a tracking report to record the results of SAEs. The principal investigator is responsible for reporting SAEs to the institutional ethics committee according to local regulations.

A SUSAR form must be used to record the details of the event, including the full description of the event, the classification of the event according to the above definitions, the judgment of the PI on the causal relationship between the SUSAR and the suspected drug, and the details of the suspected drug. All SUSAR should be reported to the leading site within 24 hours as soon as the event is recognized. The principal investigator may need to provide more details to supplement the initially reported serious adverse events, and the results of SUSAR must also be recorded. The principal investigator is responsible for reporting SUSAR to the IRB or management department according to local regulations or management requirements.

## **3. Monitoring of SAEs**

The leading center will closely monitor all SAEs to understand the relationship between

SAEs and study procedures and protocols, or the clustering of similar events in a specific location. If there are too many special SAEs related to the protocol, the study protocol needs to be revised or the trial needs to be terminated early. In addition, beyond the planned interim analysis meeting, the leading center will submit all SUSAR information to the data safety monitoring board for review.

#### **4. Monitoring of SUSAR**

The leading center will closely monitor all SUSAR to understand the relationship between SUSAR and study procedures and protocols, or the occurrence of similar events in a specific trial center. In addition, the leading center will report according to the requirements of the independent ethics committees of the participating centers.

### **IX. Quality assurance**

The study will be conducted in hospitals with acute stroke units and experience in thrombectomy. The monitor will check the data of each site and supervise the implementation of the trial. The first site monitoring visit will be conducted after the first few patients are randomized by a center, and then at least twice a year according to the number of selected patients. Through monitoring, we can ensure that investigators can strictly comply with the protocol and GCP requirements, can ensure the authenticity and reliability of the data, and ensure that all conclusions in the clinical trial are derived from the original data.

#### **1. Preservation and supervision of original data/documents**

The original documents are the basis for the true existence of the subjects and the credibility of the collected data. The original documents should be kept in each center.

The data on the case report form is from the original document and should be consistent with the source document. If there is any discrepancy, the reason should be explained.

All other data (i.e. written or electronic text records without data) can be directly

recorded on the case report form and recognized as original data.

The investigator must allow the initiator to conduct supervision, inspection, review by the ethics committee, and inspection by relevant management departments, and allow the above personnel to access all relevant original materials/documents.

The case report form and all original materials, including laboratory and other medical examination results, must be ready for review by the clinical monitor designated by the initiator at any time. The clinical monitor should check all case report forms and informed consent forms to confirm the accuracy of the data in the documents.

## **2. Preparation before the study**

Before the first participant is enrolled in the study, the representative of the study initiator should visit the center and should:

1. determine whether the facilities of the center are sufficient;
2. determine whether there are suitable enrolled patients at the study site;
3. discuss with the investigator/director of the center (and other related personnel) their responsibilities of the protocol and the study initiator or its representative, and record them in the clinical study agreement of the study initiator and the investigator/director of the center.

## **3. Site staff training**

Before the first subject is enrolled for the study, the leading site will conduct standardized training and assessment for the principal investigators and all investigators in all sites, and the study in all sites can be started only after passing the assessment. The principal investigator shall ensure that all investigators receive study-related training and make training records.

The principal investigator will keep a training record of all related personnel (doctors, nurses, and others).

## **4. Study monitoring**

During the study, the initiator will contact the site regularly, including:

1. Visit the site to provide information and support for investigators
2. Confirm that the facilities continue to meet the requirements
3. Confirm that all related personnel comply with the study protocol, the data records on the case report form are timely and accurate, and the accountability of study drugs is correct.
4. Conduct source data verification (SDV) (compare the data on the case report form to the subjects' records in the hospital and other records related to the study), including the review of the participant's informed consent. It is necessary to review all original records of each patient (such as inpatient medical records).

If the investigator or other staff of the site need to know the information and advice about the implementation of the study, they can contact the initiator of the study during the follow-up period.

When the study is completed, the monitor should ensure that each center has a plan for the long-term (15 years) preservation of relevant data and source documents.

## **5. Supervision and inspection by government regulators**

In addition, the study may also be audited by a third-party organization and by inspectors dispatched by the government administration. During and after the study, all sites must ensure that medical record report forms, original documents, and other study documents can be reviewed during the inspection auditing.

## **6. Source data**

The study sites will retain all original records and source data.

## **7. Archiving of study documents**

The investigator should abide by the principles listed in the clinical study agreement.

## **8. Study progress**

If the study procedures are not carried out according to the trial protocol, or the recruitment period is too long, the study of the site may be terminated, and the initiator of the study will also terminate the study in advance due to the safety issues in this study or other tirofiban injection studies.

## **X. Data management**

Data entry will be completed by the participating sites through the web-based data management system with password protection commissioned by the leading site. Paper case report forms will be provided to centers willing to use them for preliminary data collection.

## **XI. Statistics**

### **1. statistical considerations**

The intention to treat (ITT) principle will be applied in analyses as the full analysis set. Full analysis set: according to the basic principle of (ITT) analysis, all randomized subjects with more than one medication record and effectiveness evaluation will be included in the full analysis set. In the analysis of the full analysis set, the carry forward estimation method of the latest observation can be used for the estimation of missing values. The full analysis set is the main effectiveness evaluation population of this study.

In addition, this study will also establish a per-protocol (PP) set: including all subjects who complete the treatment specified in the protocol or do not have major protocol violations. The definition of major protocol violation will be finalized at the time of data review, which may generally include the following cases (but not limited to these

cases): serious violation of the inclusion criteria, treatment that seriously interferes with the efficacy evaluation after enrollment, serious violation of the medication dosing scheme, loss of the primary efficacy evaluation, etc.

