#### **Procedures for patients with incorrect inclusion or randomization**

If a patient who does not meet the inclusion/exclusion criteria is enrolled in this study, the following procedures should be followed:

- 1) The investigator or monitors shall immediately notify the physician of the study team to ensure the safety of patients as the primary focus.
- 2) If continuing the study treatment may endanger the safety of patients, the study treatment must be stopped. After discussion between the study team physician and the investigator, the decision will be made whether to discontinue the study drug. The reasons for discontinuing study treatment must be clearly documented. Patients should be followed up according to the specified study process, including the follow-up of endpoint events until the end of the study, in accordance with the intention-to-treat principle.
- 3) If continuation of the study is considered not to pose a risk to the patient, nor affect

the treatment of the disease, the reasons for continuing the study should be clearly recorded. Patients should continue to receive follow-up according to the planned study process.

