### ***8.3 Criteria of exclusion from data analysis***

Participants who should not be enrolled but have been enrolled, or who have completed the study but have violated some provisions of the study protocol, should be excluded from data analysis according to the investigator, including:

- (1) Those who have not used the prescribed medication.
- (2) Those without any test results after medication.
- (3) Those in whom, due to the use of forbidden drugs, the efficiency and safety cannot be evaluated.

At the blinded review meeting, the principal investigator and statistician will decide whether to eliminate cases and what data set to enter. The reasons for the exclusion should be explained, and their medical notes should be retained for future reference.

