**10. Data collection and follow-up**

The study sites are required to collect data on patients at baseline (before randomization); treatment period (day 0; the day of randomization); 24-72 hours after randomization; day 7 (or at discharge if discharged earlier) and 90 days ( $\pm 7$  days) after randomization. All SAEs including death within the 3-month follow-up period are recorded. The assessments at 90-days are to be undertaken by a well-trained investigator, who is blind to treatment allocation, either face to face or by telephone. Source documents, such as patient interview records or questionnaire responses, can be directly entered into the database. Paper case report forms can also be filled in and retained as source documents. Brain imaging will be collected at baseline, during the treatment period, and 24-72 hours ( $\pm 8$  hours). If clinically indicated, patients may receive further brain imaging scans at a later stage. Brain imaging data are collected by each site. The leading site assists each site in uploading image data. After uploading, the leading site is responsible for image analysis.

90-day follow-up is required for all participants in this study. If they die before 90 days, they will be followed up until death. Patients who do not comply with the protocol

and/or terminate the assigned treatment regimen also need to be followed up for 90 days, as their data will be required for the intention-to-treat analysis. The study flow chart lists the types of data and the schedule of evaluation. The leading site will provide the paper version of the case report form and the instruction manual for reference, as well as the guidelines of the case report form and the definition of terms.

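### The main efficacy set is labelled intention-to-treat, but entry depends on medication records and an evaluation after randomization, and the section 8.3 exclusions are not confined to the per-protocol set

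*Protocol*

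**What the plan says.** Section 1 of XI. Statistics opens with "The intention to treat (ITT) principle will be applied in analyses as the full analysis set". It then sets the entry rule: "all randomized subjects with more than one medication record and effectiveness evaluation will be included in the full analysis set". It gives that set its role: "The full analysis set is the main effectiveness evaluation population of this study". A per-protocol set is defined separately in the same section, and carry-forward of the latest observation is allowed for missing values in the full analysis set.

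Section VI.8.3 says that patients enrolled in error, and patients who completed the study but broke some of its provisions, "should be excluded from data analysis according to the investigator". It lists three groups:

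- "Those who have not used the prescribed medication";
- patients with no test results after medication;
- patients whose efficacy and safety cannot be evaluated because they took a prohibited drug.

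The principal investigator and the statistician settle eliminations and data sets at a blinded review meeting.

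Two other places point the other way. The procedures for incorrect inclusion or randomization (VI.6.1) keep wrongly enrolled patients in follow-up. For those whose study treatment is stopped, they do so "in accordance with the intention-to-treat principle". Section VI.10 follows patients who do not comply or who stop their assigned regimen to 90 days, "as their data will be required for the intention-to-treat analysis".

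**The concern.** An intention-to-treat set is fixed by randomization. This one is fixed by what is recorded afterwards, in an open-label trial where only one arm is prescribed a study drug (VI.7.2). A condition on dosing therefore does not act equally on the two arms. If controls are exempted from it, as they must be for the analysis to exist, only tirofiban patients can be removed by it. Patients who miss the drug after randomization may differ in prognosis from the rest of their arm, and no corresponding controls are removed. The comparison is then no longer between the groups that randomization formed.

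The protocol also gives the analyst two instructions that cannot both be followed. A tirofiban patient who was never dosed is needed for the analysis under VI.10 and excluded from it under VI.8.3. The choice affects the population of the primary test and could be made after the data are in.

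**Working it through.** **1. The texts side by side**

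| Patient | XI.1 and VI.8.3 | VI.6.1 and VI.10 |
|---|---|---|
| Randomized to tirofiban, not dosed | Fails the medication condition; listed for exclusion | Followed to 90 days for intention-to-treat |
| Wrongly enrolled | Listed for exclusion | Kept in follow-up; intention-to-treat cited when treatment is stopped |
| Randomized to control, no study drug | Cannot be held to a study-drug condition | Kept |

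**2. The plan's own figure.** Inputs from XI.4: 70% against 50%, two-sided alpha 0.05, power 80%, 7% dropout. The chi-square formula without continuity correction gives

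n = [1.96·√(2·0.6·0.4) + 0.8416·√(0.7·0.3 + 0.5·0.5)]² / 0.2² = (1.358 + 0.571)² / 0.04 ≈ 93 per arm.

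Then 93/0.93 = 100 per arm, 200 in total. The stated size is reproduced, so this point does not touch the sample size arithmetic.

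**3. Effect of one-sided exclusion when there is no true effect.** Take 50% success in both arms of 100 (the planned control rate). Drop k tirofiban patients whose success rate is r, and no controls. Both k and r are assumptions; the documents give neither.

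- m = 100 − k; p_T = (50 − k·r)/m; d = p_T − 0.50
- pooled rate p̄ = (m·p_T + 50)/(m + 100)
- SE0 = √[p̄(1 − p̄)(1/m + 1/100)]; SE1 = √[p_T(1 − p_T)/m + 0.25/100]
- rejection probability = 1 − Φ((1.96·SE0 − d)/SE1) + Φ((−1.96·SE0 − d)/SE1)

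Example, k = 7 and r = 0: p_T = 50/93 = 0.538, d = 0.038, SE0 = 0.0720, SE1 = 0.0719. The two tails are about 0.075 and 0.0065, together about 8.2%.

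| k dropped | r = 0: rate, type I error | r = 25%: rate, type I error | r = 50% |
|---|---|---|---|
| 5 | 52.6%, 6.6% | 51.3%, 5.4% | 50%, 5.0% |
| 7 | 53.8%, 8.2% | 51.9%, 5.8% | 50%, 5.0% |
| 10 | 55.6%, 11.9% | 52.8%, 6.7% | 50%, 5.0% |

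**4. Effect under the planned difference.** Suppose that k undosed tirofiban patients have the control rate of 50% (again an assumption). For k = 7, the rate in the arm as randomized is (93·0.70 + 7·0.50)/100 = 68.6%, with power 76.7%. The set that drops them keeps 70% and shows 81.4%. For k = 5 the figures are 69.0% with 78.6%, against 81.8%. For k = 10 they are 68.0% with 73.8%, against 80.7%. With nobody undosed, analysing all 200 gives 82.8%.

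**The case against.** The best defence is that the wording is looser than it looks and that a blinded review stands between it and the data. Several stronger readings that a reader might infer are indeed not supported.

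- *That no control would qualify, or that a bolus-only patient has a single record and drops out.* The protocol does not define a medication record. Concomitant drugs are recorded for everyone (VI.10.4 and the study flow chart), and the bolus and infusion entries are not counted as records anywhere. The phrase may also stand for at least one record. None of these readings turns the set into all randomized patients, and item (1) of VI.8.3 remains in any case.
- *That patients who die early or in whom access fails are lost from the full analysis set.* The entry rule asks for an effectiveness evaluation, not the primary one. XI.1 lists loss of the primary evaluation as a reason for leaving the per-protocol set, and VI.9 and VI.10 provide a 90-day or death outcome for every patient. The real gap is that the protocol does not say how the primary outcome is scored for them.
- *That every user of a prohibited drug is excluded.* Item (3) applies only where efficacy and safety cannot be evaluated. It and the missing-result item can affect either arm.
- *That the bias favours tirofiban, with an error near 8%.* That figure places the whole 7% dropout allowance in one arm, although XI.4 applies it to both, and counts every such patient as a failure. If the excluded patients did better than their arm, the sign would reverse.

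The blinded review is a genuine safeguard and could be read as sorting cases between the two sets. It helps only partly: VI.8.3 speaks of exclusion from data analysis without naming a set, and the fact that a patient was due the drug and did not receive it reveals the arm.

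**Conclusion.** The point holds in this form. The main efficacy population is called intention-to-treat but depends on records made after randomization. Section VI.8.3 adds exclusions that are not confined to the per-protocol set, and VI.6.1 and VI.10 contradict both. In any workable reading, the study-drug condition can be failed only in the tirofiban arm.

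The contradiction and the arm-specific condition are established from the text. The size and direction of any bias are not. They rest on the assumed number and outcomes of the patients dropped, and run from no bias, through a type I error of about 5.4% to 6.7% (a quarter successes, 5 to 10 dropped), to an upper bound of 6.6% to 11.9% (all failures). This should be corrected because it governs the primary test, not because a particular bias has been shown.

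**What to change.** 1. Define the main analysis set in XI.1 as all randomized patients with valid consent, analysed in the assigned arm whatever drug was received or procedure done. Remove the medication-record and evaluation conditions.
2. State how the primary outcome is scored when there is no angiogram after a first pass because no pass could be made: count it as not achieved. Except patients whose first angiogram already shows mTICI 2b or better, which VI.9 counts as first-pass recanalization; the requirement of no symptomatic hemorrhage still applies to them.
3. Confine the exclusions in VI.8.3 to the per-protocol set, so that they agree with VI.6.1 and VI.10.

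The cost is wording in the protocol and in any analysis plan that follows it. The sample size stays at 200. The observed effect may be slightly smaller, for example 18.6 instead of 20 points (68.6% against 50%) if 7 of 100 tirofiban patients go undosed and have the control rate.
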